**Methods:**

This is a multisite, single-dose, double-blind, randomized, placebo-controlled, 4-period, 4-way crossover, pharmacodynamic (PD) and pharmacokinetic (PK) study in healthy subjects. Neurophysiological biomarkers of spinal and brainstem activity (the RIII flexion reflex, the N13 component of somatosensory evoked potentials (SEP) and the R2 component of the blink reflex) will be recorded before and at three distinct time points after administration of three medications known to act on the nociceptive system (lacosamide, pregabalin, tapentadol), and placebo, given as a single oral dose in separate study periods. Medication effects on neurophysiological measures will be assessed in a clinically relevant hyperalgesic condition (high-frequency electrical stimulation of the skin), and in a non-sensitized normal condition. Patient-reported outcome measures (pain ratings and predictive psychological traits) will also be collected; and blood samples will be taken for pharmacokinetic modelling. A sequentially rejective multiple testing approach will be used with overall alpha error of the primary analysis split between the two primary endpoints, namely the percentage amplitude changes of the RIII area and N13 amplitude under tapentadol. Remaining treatment arm effects on RIII, N13 and R2 recovery cycle are key secondary confirmatory analyses. Complex statistical analyses and PK-PD modelling are exploratory.

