**Key secondary analyses of the primary endpoints:**	
1. To test if the percentage of change of the RIII area of the flexion reflex at the time point t60 post-drug administration vs the pre-drug time point, differs in the pregabalin and/or lacosamide period as compared to the placebo period, at the sensitized lower limb.	
2. To test if the percentage of change of the N13-SEP amplitude at the time point t60 post-drug administration vs the pre-drug time point, differs in the pregabalin and/or lacosamide period as compared to the placebo period, at the sensitized upper arm.	
3. To test if the percentage of change of the R2 recovery cycle at 500 ms interstimulus time interval at the time point T60 post-drug administration vs the pre-drug administration differs in the tapentadol, pregabalin and/or lacosamide periods as compared to the placebo period.	

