#### Definition of the primary endpoints

RIII flexion reflex change endpoint data being repeated measurements across the four periods will be analyzed with a mixed effect model with treatment (4 levels), period (4 levels), and center and sequence as fixed effects. The variance-covariance structure for the repeated measure variable period should be chosen as UN (unstructured), TOEPH (heterogeneous Toeplitz), CSH (heterogeneous compound symmetry), ARH(1) (heterogeneous AR(1)), TOEP (Toeplitz), CS (compound symmetry), and AR(1) (first order autoregressive) in that order of preference.

The least squares (LS) mean difference of treatment active treatment versus placebo will be estimated based on this model and the estimate as well as the corresponding unadjusted confidence interval and *p*-value will be provided.

The analysis for the N13-SEP change is similar and details will be provided in the analysis plan.

If either (or both) of the primary endpoints’ tests show significant differences between tapentadol and placebo, in the sense that the *p*-value is below the corresponding local alpha level, the differences are confirmed and the testing procedure continues according to the graph above.

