### Definition of secondary endpoints

These statistical analyses are considered confirmatory only provided they have received local *α*-levels (type I error greater than 0) from prior tests rejecting their corresponding null hypotheses. The method for testing the secondary endpoints comparing the other treatment groups versus placebo mirrors the model specifications of the primary analysis above but using the Dunnett-adjusted estimation and testing results to compare pregabalin and lacosamide with placebo respectively. The method for testing the key secondary endpoint for R2 recovery cycle is identical to the specifications of the primary analysis above.

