According to the sequentially rejective multiple testing design, two primary endpoints will be tested simultaneously at alpha/2; these are pairwise comparisons of one medication vs. placebo for one post-medication time point and one readout variable that are most likely to be significant, based on published literature (see power calculation). Three key secondary endpoints are assessed, given that alpha levels were passed successfully from one or both of the primary endpoints or from one or both of the other key secondary endpoints. All efficacy analyses will be done on data pooled across participating centers; efficiency of this multicenter study approach in human volunteers will be assessed by comparing across-center vs. within-center variability of the various readout variables.

In addition to the analysis of the individual RCTs, biomarker results and pharmacokinetic and pharmacodynamics analyses will be compared across trials and to preclinical studies and will possibly try to establish a latent variable model of underlying mechanisms at peripheral, spinal, and brain levels. Pain ratings will be included as another readout variable, and questionnaires on psychological traits predictors (e.g., catastrophizing, anxiety) will also be analyzed as potential predictors of pain and analgesia. By identifying specific mechanisms within different compartments of the nociceptive system in healthy volunteers, these same quantitative neurophysiological biomarkers, if well validated against clinically meaningful outcomes in patients, may be used for patient stratification and enrichment in later clinical trials, as encouraged by the recent EMA/CHMP/970057/2011 Guideline. This will accelerate the development of novel analgesics in several ways: preclinical prediction will be improved by using translatable readouts across species; clinical Phase 1 trials will benefit from biomarkers of target engagement and from human surrogate models predictive of clinical efficacy; clinical Phase 2 and 3 studies will benefit from tools for patient stratification.

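### R2 recovery cycle is a confirmatory key secondary with three drug–placebo contrasts, but the article assigns it the primaries' unadjusted, single-contrast method

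*Protocol article*

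**What the plan says.** Table 4, third item under the key secondary analyses, asks whether the percentage change in the R2 recovery cycle (500 ms interval, 60 minutes after dosing) "differs in the tapentadol, pregabalin and/or lacosamide periods as compared to the placebo period". That is three contrasts, and the and/or wording lets any one of them count. The Abstract gives them confirmatory standing: "Remaining treatment arm effects on RIII, N13 and R2 recovery cycle are key secondary confirmatory analyses". The section Definition of secondary endpoints makes that standing conditional on alpha having been received from an earlier rejection.

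The same section sets the method. For the drugs other than tapentadol it mirrors the primary model, "using the Dunnett-adjusted estimation and testing results to compare pregabalin and lacosamide with placebo respectively". It then gives R2 a sentence of its own: "The method for testing the key secondary endpoint for R2 recovery cycle is identical to the specifications of the primary analysis above".

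The section Definition of the primary endpoints describes that analysis. A mixed model yields LS mean differences from placebo, and "the corresponding unadjusted confidence interval and *p*-value will be provided". A primary succeeds if its test is found to "show significant differences between tapentadol and placebo", with the p-value set against the local alpha. Each primary therefore has one confirmatory contrast.

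The Statistical methods section {20a} gives each primary half of the overall alpha and passes alpha on by weights shown in Fig. 3. The Discussion says: "Three key secondary endpoints are assessed, given that alpha levels were passed successfully". The three are RIII, N13 and R2, and they may receive alpha from the primaries or from one another.

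**The concern.** An unadjusted p-value is right for a primary because each primary has one contrast. Carried over to R2, the same rule covers three contrasts, so the endpoint with the most comparisons is the only multi-drug one with no stated correction. The graphical procedure controls the family-wise error only if the test at each node holds the local level given to that node. Three unadjusted tests at one local alpha do not.

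Gatekeeping does not remove the problem. It bites when a primary has a real effect and opens the R2 step, and the Sample size section expects a tapentadol effect on RIII. At stake is a confirmatory statement that some drug changes brainstem excitability when none does. Because the Discussion lets key secondaries pass alpha to one another, a false R2 rejection could also release alpha to the others.

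**Working it through.** **Inputs from the article.** Three R2 contrasts (Table 4); an unadjusted p-value against the local alpha (Definition of the primary endpoints, carried to R2 by Definition of secondary endpoints); one R2 endpoint among three key secondaries (Discussion); alpha/2 per primary (Statistical methods).

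**Assumptions.** Overall alpha is 0.05 two-sided, since the article prints no number. R2 is one node in the graph. The three contrasts share the placebo period: with equal variances and equal within-subject covariances, the covariance of two contrasts is half the variance of each, so the correlation is 0.5.

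**The plan's own figure.** Alpha/2 + alpha/2 = 0.025 + 0.025 = 0.05. The split between the primaries is sound.

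**The R2 step.** With local alpha a, critical value c = z(1 − a/2) and correlation ρ, the chance of at least one false claim when all three R2 nulls are true is

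1 − ∫ φ(x) [Φ((c − √ρ·x)/√(1−ρ)) − Φ((−c − √ρ·x)/√(1−ρ))]³ dx.

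| Local alpha a | c | ρ = 0.5 | Ratio to a | ρ = 0.8 | ρ = 0 | Bound 3a |
|---|---|---|---|---|---|---|
| 0.0125 | 2.498 | 0.0338 | 2.70 | 0.0269 | 0.0370 | 0.0375 |
| 0.025 | 2.241 | 0.0655 | 2.62 | 0.0516 | 0.0731 | 0.0750 |
| 0.05 | 1.960 | 0.1254 | 2.51 | 0.0982 | 0.1426 | 0.1500 |

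Simulation with finite degrees of freedom agrees: 0.0334, 0.0650 and 0.1245 with 40 subjects; 0.0339, 0.0659 and 0.1255 with 56.

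If one drug truly affects R2 and two do not, the same formula with exponent 2 gives 0.0236, 0.0465 and 0.0907, still nearly twice the local alpha.

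**Against the overall alpha.** Setting the formula equal to 0.05 at ρ = 0.5 gives a = 0.0188, and 0.0188/0.05 = 38% of the overall alpha. With a quarter of alpha at R2 the step gives 0.0338, with a third 0.0445, with half 0.0655, with all of it 0.1254. These rates are conditional on the step having been opened; they become unconditional only as the power of the primaries approaches 1.

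**Alternative readings of the R2 sentence.**
- Tapentadol only: one contrast, so the error equals a. Table 4 and the Abstract are then contradicted, and two confirmatory R2 comparisons have no method.
- Dunnett for pregabalin and lacosamide, tapentadol unadjusted: 0.0235, 0.0460 and 0.0897 at the three local levels, still above each.

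**After a three-contrast Dunnett test.** The error equals a. The critical |z| is 2.843, 2.607 and 2.349 for a = 0.0125, 0.025 and 0.05, which means a nominal p below 0.0045, 0.0091 and 0.0188 for a single contrast.

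**The case against.** The exact graph is in Fig. 3, which is not available here. The Discussion counts endpoints, not hypotheses. If Fig. 3 gives each R2 drug contrast its own weighted node, unadjusted p-values against those local levels are correct and there is no inflation. This stands: it is why confidence is moderate and why the size is stated conditionally.

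A reader might infer that the R2 step breaks the whole trial's error rate. The documents do not support that as a finding. It needs an overall alpha that is never printed and a local R2 level above about 0.019, which depends on the unseen weights; at a quarter or a third of alpha the step stays below 5%. Since RIII and N13 also receive alpha, 0.025 or more at R2 is plausible but not established.

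The R2 sentence may refer only to the mixed model, or only to tapentadol. Either is possible, but the first leaves three confirmatory contrasts with no rule and the second conflicts with Table 4. Both need a correction.

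Details are deferred to the analysis plan, the trial is called exploratory under Trial design, and the primary tests are untouched. That lowers the severity. It does not excuse the sentence: it states a rule rather than deferring one, and an analysis plan that follows it inherits the problem.

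**Conclusion.** The article names three confirmatory R2 contrasts and assigns them a method built for one, with no adjustment or order stated for them in the text. If R2 is one step with one local alpha, its false-claim rate is about 2.5 to 2.7 times that alpha at correlation 0.5 (about 2.0 to 2.2 times at 0.8, 2.9 to 3.0 times at 0), given that the step has been opened and no drug affects R2. The excess over the step's own local alpha holds at every weight; an excess over the trial's overall alpha is possible but not shown. The tapentadol-only reading controls the error at the price of contradicting Table 4. The point should be fixed, with moderate confidence, because Fig. 3 could resolve the multiplicity question.

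**What to change.** Before unblinding, replace the last sentence of Definition of secondary endpoints, in the protocol and the analysis plan, by one of the following:

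- R2 at 500 ms is analysed with the primary model, and Dunnett-adjusted p-values over the three drug–placebo contrasts are compared with the R2 local alpha.
- Each R2 contrast is a separate hypothesis in the graph with its own weight; show this in Fig. 3 and say so in the text.
- If only tapentadol is meant to be confirmatory for R2, correct Table 4 item 3 and the Abstract to match.

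Holm, or a fixed order of the three drugs, within the R2 step would also hold the level.

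The cost is a sentence or two of text; data collection and sample size are unchanged. The statistical price of the Dunnett option is that a single R2 contrast needs a nominal p below about 0.009 at local alpha 0.025, or about 0.019 at local alpha 0.05, so power for any one drug on R2 falls.

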### Interim analyses {21b}

No interim analysis is foreseen for this study.

### Methods for additional analyses (e.g., subgroup analyses) {20b}

The methods for additional analyses are the same as described in the protocol for our related trial [IMI2-PainCare-BioPain-RCT3] see [2] for more details. Briefly, several additional exploratory analyses will be done, such as variants of primary endpoint parameter extraction, additional functional biomarkers extracted from the recorded signals, item analyses of PROMs, pharmacokinetic-pharmacodynamic modelling, complex hierarchical modelling, estimation of variance, and effect size of candidate endpoints for future clinical trials. These are described in the statistical analysis plan.

The data collected in this trial, together with the data from the other three IMI2-PainCare-BioPain-RCTs and the preclinical studies of the BioPain project, will be subject to pharmacometric analyses with the intention to validate biomarkers that can translate from preclinical to clinical readouts [2]. As both drug concentrations and biomarker responses are measured at several time points post-drug administration, the relationship between drug levels and selected biomarkers will be explored and modelled. The pharmacometric analysis will be described in a separate pharmacometric analysis plan and will consist briefly in developing population pharmacokinetic/pharmacokinetic (PK/PD) models estimating the primary PK parameters (i.e., apparent volume of distribution, and total plasma clearance), the primary PD parameters (i.e., C50, the plasma or effect site concentration that elicits a response equal to half of the maximum attainable effect (EMAX), and their associated inter-individual variability.

Analyses of demographic data and other baseline characteristics will consist of descriptive summary statistics. While these tables may provide the summaries by groups (i.e., treatment sequences), there will be no statistical tests conducted on baseline characteristic differences. Data will also be listed. Details will be provided in the statistical analysis plan.

A reliability analysis will investigate the biomarker and their measurement characteristics using the following concepts, all based on the full analysis set. Detailed specifications will be provided in the statistical analysis plan. Assessment of the repeatability of a (individual) biomarker response measurement method will use the statistics described by Bland & Altman [34] (such as differences against means plots). Also, within and between subject variabilities will be estimated using the mixed AN(C)OVA models including the corresponding variance components according to the repeated measurements design. These include data across time points within a “visit” (e.g., during placebo treatment period) or across “visits” (e.g., baseline measurements across the treatments periods) as applicable. Should measurement methods of the same biomarker be compared the agreement statistics of Bland and Altman will be used. Assessment of the reproducibility will follow the statistics (such as difference limits, minimum significant difference, limits of agreement, etc.) as described in standard guidance documents. As applicable, further statistics presented for test-retest characteristics may include correlations (such as concordance correlation coefficients, intraclass correlation coefficients), coefficients of variations, and sensitivity to change statistics, e.g., smallest real difference.

Any changes to the planned statistical analyses, if considered prior to unblinding, will be described and justified in an amendment to the protocol (if study is still ongoing) and to the statistical analysis plan. Deviations from planned analyses will also be explained in the final study report.

### Methods in analysis to handle protocol non-adherence and any statistical methods to handle missing data {20c}

The methods in analysis to handle protocol non-adherence and any statistical methods to handle missing data are the same as described in the protocol for our related trial [IMI2-PainCare-BioPain-RCT3] see [2] for more details.

### Plans to give access to the full protocol, participant-level data, and statistical code {31c}

This will be determined at the end of the project period of IMI-PainCare.

## Oversight and monitoring

### Composition of the coordinating center and trial steering committee {5d}

The composition of the coordinating centre and trial steering committee are similar to the ones described in the protocol for our related trial [IMI2-PainCare-BioPain-RCT3] see [2] for more details. Briefly, this trial is part of the Biopain subtopic of the IMI2 PainCare project.

The PainCare Innovative Medicines Initiative (www.imi-paincare.eu) is a partnership between the European Union and the European pharmaceutical industry. IMI facilitates open collaboration in research to advance the development of and accelerate patient access to personalized medicines for the health and well-being of all, especially in areas of unmet medical need.

The overall coordination of the IMI-PainCare project is performed by the Project Coordinator who acts simultaneously as Co-Lead for the subproject BioPain including the IMI2-PainCare-BioPain RCTs ([name], Heidelberg University, Germany).

The RCT Lead will act as the international coordinating investigator who is responsible for the coordination of the Principal Investigators at multiple trial sites in multiple countries. The RCT Lead will be sponsor of the study ([name], Sapienza University of Rome).

There will be one Principal Investigator at each trial site. If, at the trial site, the trial is conducted by a team of individuals, the investigator leading and responsible for the team is called the Principal Investigator, and the other individuals of the team are called investigators.

IMI PainCare project has been approved under the condition that the consortium carrying out the project implements an external ethics advisory board which (1) reviews the proper application of the relevant laws and guidelines containing ethical rules and the H2020 rules by the investigators; (2) provides advice to and monitors the activities of the investigators with regard to ethical issues; and (3) provides advice on the compliance with European ethical laws and regulations and with different guidelines, laws, and regulations of countries where studies are being performed. Practical implementation: ConsulTech, non-clinical partner of the study, will collect all relevant ethical documents and will ensure that all partners submit them on time. ConsulTech will then draw up a questionnaire for the ethics advisory board, which will allow it to check whether all important ethical requirements and documents have been submitted and that all legal guidelines have been adhered to.

### Composition of the data monitoring committee, its role and reporting structure {21a}

A data monitoring committee is not foreseen. Data management will be performed by the Heidelberg University Computing Centre. Documentation of the responsibilities and delegation thereof will be maintained in the trial master file. All aspects of the data management process are described in the Data Management Plan.

### Adverse event reporting and harms {22}

Adverse events will be documented from the time of enrollment up to the time of the last protocol scheduled contact. Subjects in the trial have the opportunity to report adverse events spontaneously. There will also be given a general incitement for events. Date of onset and termination for each adverse event, and impact of the test substance will be registered. The severity of the adverse event and the relationship between the treatment drug and the adverse event will be assessed as previously extensively described [2]. Investigators will report all serious adverse events to the sponsor as soon as possible and within 24 h, in order to report to the Competent Authority (CA) and the IEC. Handling of adverse events will follow GCP and applicable regulations as described previously [2].

### Frequency and plans for auditing trial conduct {23}

The frequency and plans for auditing trial conduct are similar to the ones described in the protocol for our related trial [IMI2-PainCare-BioPain-RCT3] see [2] for more details.

### Plans for communicating important protocol amendments to relevant parties (e.g., trial subjects, ethical committees) {25}

Any modifications to the protocol which may impact on the conduct of the study, potential benefit of the subject or may affect subject’s safety, including changes of study objectives, study design, subject population, sample sizes, study procedures, or significant administrative aspects will require a formal amendment to the protocol. Such amendment will be approved by the IEC and prior to implementation and notified to the health authorities in accordance with local regulations [2].

### Dissemination plans {31a}

A final report integrating trial results will be prepared. The Principal Investigator will provide the competent authority/ies and relevant IEC(s) with a summary of the trial results in accordance with applicable regulatory requirements.

The results of this trial will be publicly disclosed (EudraCT). The results (or parts thereof) of this trial will be published according to the Grant Agreement and Consortium Agreement of IMI-PainCare (grant No 777 500).

